### Additional analyses

The methods used for statistical analyses will also be used for additional analyses of primary and secondary outcomes. Intention-to-treat basis will be used to conduct statistical analysis. The analyses of the outcomes will be analyzed as randomized, regardless of protocol adherence. All variables will be screened for frequency and type of missingness. If missingness is > 5% for any variable, the mean normal value of the patient group will be used for imputation.

No formal interim analysis of primary and secondary outcomes is planned.

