### Sample size

According to previous studies, the incidence rate of POCD after a major surgery was 25% [12], and the estimated application of probiotics could reduce it to 10%. According to alpha = 0.05, Power = 0.80, PASS 11 will be applied. The calculated sample size is *n* = 100 cases, with a shedding rate of 10%. The sample size of each group is *n* = 110 cases.

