### Statistical analysis

All statistical tests are conducted by two-sided test, and the difference tested will be considered to be statistically significant if *P* ≤ 0.05(unless otherwise specified). The primary outcome measure will be statistically analyzed by chi-square or Fisher exact probability. Secondary outcome measures will be tested by group t-test. The description of quantitative indicators will calculate the mean, standard deviation, median, minimum, and maximum. The number and percentage of patients are used to statistically describe the demographic information, medical history, combined diseases and symptoms, physical examination, operation time, etc. According to the numerical characteristics of variables, *t*-test/Wilcoxon rank sum test is used to compare the quantitative data of age, height, and weight between the two groups; chi-square test/exact probability method is used to compare the categorical variables such as gender, medical history, combined diseases and symptoms, physical examination and so on.

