### Outcome measures

#### Primary outcome measures

Our primary objective is to assess the incidence of POCD 7 days after surgery. The assessment of cognitive function was completed 1 day before operation and 7 days after operation or on the day of discharge by the following scales: digit span test, digit symbol test, Wechsler Memory Scale (WMS), visual regeneration, and digital connection test. The POCD was defined as follows:

The data of each patient consists of preoperative and postoperative data. The *Z*-score is used to determine whether the patient had POCD [13]. The positive result is at least one *Z*-score ≤ 2 (Wechsler word recall, visual reproduction, number symbols, number width) or ≥ 2 (number lines).

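### The single-mean imputation rule gives no valid value for the yes/no POCD endpoint, and its effect on the primary and TICS-m results turns on choices the plan leaves open

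*Protocol article*

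**What the plan says.** Under Additional analyses, the protocol article fixes one rule for missing data: "If missingness is > 5% for any variable, the mean normal value of the patient group will be used for imputation". It also commits to analysing outcomes as randomized, so patients with missing values stay in the denominator and their filled-in values count.

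Under Sample size, it plans "with a shedding rate of 10" percent, which is twice the 5% trigger.

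Under Primary outcome measures, POCD is a yes/no status. A patient is positive if at least one test's Z-score passes a cut-off of 2, using test results from before and after surgery ("The data of each patient consists of preoperative and postoperative data"). Under Statistical analysis, the primary outcome is compared by chi-square or Fisher's exact test and secondary outcomes by t-test. Of the two listed secondary outcomes, only the 1-month TICS-m score is continuous.

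The rule does not say whether the filled-in quantity is a raw score, a Z-score or POCD status, whether the patient group is one arm or everyone, or what normal means. The article names no missing-data sensitivity analysis.

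**The concern.** The plan states this method; it has not simply left the matter to an analysis plan, and an analysis plan that followed it would inherit the fault. There are two problems.

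- **Primary endpoint.** The mean of a yes/no variable is a fraction, which is not a possible value for one patient. Moving the rule down to the component tests only shifts the difficulty, because the result then depends on which component is filled in. On the most natural reading, a patient with no day-7 assessment is given an average result and counted as free of POCD. Patients too unwell or confused for a test battery are plausibly over-represented among the missing.
- **Continuous outcome.** A filled-in mean is treated as an observation. It adds to the sample size and contributes no variance, so precision can be overstated.

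At stake are the size of the reported POCD incidences, the false-positive rate of the primary comparison if the arms lose patients unequally, and the false-positive rate of the TICS-m t-test.

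**Working it through.** **Inputs from the documents.** Control POCD: "the incidence rate of POCD after a major surgery was 25" percent. Probiotic: "the estimated application of probiotics could reduce it to 10" percent. Error rates: "According to alpha = 0.05, Power = 0.80, PASS 11 will be applied". Sidedness: "All statistical tests are conducted by two-sided test". Allocation is 1:1 with 110 per group; loss is 10%.

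**Plan's own figure.** With the pooled-variance formula, mean rate 0.175:

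n = [1.96·√(2·0.175·0.825) + 0.8416·√(0.25·0.75 + 0.10·0.90)]² / 0.15² = 99.5, so 100 per group.

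This reproduces the stated 100. Dividing by 0.90 gives 112 against the stated 110, a negligible gap. The sample size is not in dispute. At 10% loss, 110·0.90 = 99 completers per arm remain, with power 79.8%.

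**Primary endpoint, normal value filled in at Z-score level.** A Z near 0 does not pass −2 (or +2 for the number-line test), so every missing patient is recorded as POCD-free.

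- *Equal 10% missing, unrelated to POCD.* Rates become 0.25·0.90 = 22.5% and 0.10·0.90 = 9.0%, and the difference falls from 15.0 to 13.5 points. The nominal standard error is √(0.225·0.775/110 + 0.09·0.91/110) = 0.0483, against √(0.25·0.75/99 + 0.10·0.90/99) = 0.0529 in completers. Power is 78.9% against 79.8%.
- *Type I error.* True POCD is set at 25% in both arms, 110 per arm, missingness unrelated to POCD, by exact enumeration of the chi-square test. The unequal splits are assumptions.

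| Missing, arm 1 / arm 2 | Recorded rates | Type I error |
|---|---|---|
| 10% / 10% | 22.5% / 22.5% | 4.9% |
| 5% / 15% | 23.75% / 21.25% | 7.1% |
| 2% / 18% | 24.5% / 20.5% | 10.7% |
| 0% / 20% | 25.0% / 20.0% | 14.2% |

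- *Missingness related to POCD.* Assume 5% missing in control, 15% in probiotic, and half of the missing with POCD. Recorded rates are 0.25 − 0.05·0.5 = 22.5% and 0.25 − 0.15·0.5 = 17.5%, and the test rejects about 15% of the time, almost always in favour of probiotics. A complete-case analysis of the same scenario compares 0.225/0.95 = 23.7% with 0.175/0.85 = 20.6% and already rejects about 8% of the time.

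**Primary endpoint, raw postoperative score filled in.** The patient's own baseline is kept. Assume Z is the change divided by the SD of change, equal pre and post SDs, and pre/post correlation r. The change is then the group mean minus the patient's baseline, and P(Z ≤ −2) = Φ(−2·√(2(1−r))). For r = 0.5 this is 2.3% per test; for r = 0.9 it is 18.6%. Over five tests treated as independent, 1 − (1−p)⁵ gives 11% to 64% flagged. Who is flagged depends only on how well the patient scored before surgery, not on what happened afterwards.

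**TICS-m by t-test, 10% missing (99 of 110 observed).**

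- *Own-arm mean.* Reported over correct standard error = √(98/109)·√(99/110) = 0.8995. True alpha = 2·[1 − Φ(1.96·0.8995)] = 7.8%; a simulation of 40,000 trials gives 7.7%. At 20% missing it is about 11.8%.
- *Mean of both arms combined.* Simulated alpha is 4.7% to 5.1% for 6% to 20% missing. The difference shrinks by the missing fraction, to 0.90 of its value at 10% missing.

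**The case against.** The strongest reply is that the damage at the planned loss is small and that the worst figures need assumptions the document does not contain. Much of this stands.

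- With balanced 10% loss unrelated to POCD, the primary test keeps its type I error and loses under one point of power.
- A reader might infer that the rule always classes missing patients as POCD-free. The text does not support that. It requires filling in at Z-score level and a cut-off of −2. The article prints the cut-off without a minus sign, and taken literally a Z of 0 would count as POCD. With raw-score filling, some missing patients are flagged.
- A reader might also infer that t-tests on imputed data always exceed 5%. That holds for own-arm means only. The wording can equally mean all patients, and then alpha stays near 5%.
- The 15% false-benefit figure cannot be charged to the rule alone. It assumes unequal, outcome-related missingness, which already gives about 8% in completers.
- The 10% is overall loss. The primary battery may be done on the day of discharge, so early discharge need not leave it missing. The trigger is more secure for the 1-month telephone outcome.

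The reply does not rescue the rule. Its effect differs by reading because the plan does not fix the reading, and no reading yields a valid single value for a thresholded endpoint or carries the uncertainty of the imputation.

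**Conclusion.** The point holds in conditional form. The single-mean rule is a stated, poorly chosen method, likely to be triggered for TICS-m and plausibly for the day-7 tests.

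For the primary endpoint on the Z-score reading, it lowers both recorded incidences by the missing fraction. It is close to harmless for the test when loss is balanced, and inflates type I error to about 7% to 11% under the assumed 5%/15% and 2%/18% splits, more if missingness is related to POCD. On the raw-score reading, classification is arbitrary. For TICS-m, it understates the standard error by about 10% with own-arm means, or dilutes the difference with a combined mean.

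The documents do not establish that the primary result will be biased in a given direction, because neither the reading nor the pattern of missingness is known. The arithmetic is firm; the missingness splits, correlations and independence are assumptions.

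**What to change.** Delete the mean-imputation rule and its 5% trigger, so that one approach applies whatever the missing percentage. In its place:

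1. Multiply impute the individual test scores, with at least arm and baseline scores in the model; derive POCD within each completed data set; combine by Rubin's rules. Treat TICS-m in the same way.
2. Report a complete-case analysis alongside.
3. Add a sensitivity analysis counting missing patients as POCD in both arms. Multiple imputation alone does not remove bias when missingness depends on the unobserved outcome. This analysis is a bound rather than a better estimate: in the outcome-related scenario above it rejects about 13% of the time, in the opposite direction.

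If the sponsor prefers to leave the imputation model to the analysis plan, the protocol should at least withdraw the present rule and state that scores, not POCD status, are imputed.

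The cost is a wording change and a little more programming, with no change to sample size, visits or data collection. It should be made before unblinding.

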### Outcome measures

#### Primary outcome measures

Our primary objective is to assess the incidence of POCD 7 days after surgery. The assessment of cognitive function was completed 1 day before operation and 7 days after operation or on the day of discharge by the following scales: digit span test, digit symbol test, Wechsler Memory Scale (WMS), visual regeneration, and digital connection test. The POCD was defined as follows:

The data of each patient consists of preoperative and postoperative data. The *Z*-score is used to determine whether the patient had POCD [13]. The positive result is at least one *Z*-score ≤ 2 (Wechsler word recall, visual reproduction, number symbols, number width) or ≥ 2 (number lines).

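### The POCD cut-off is printed as Z ≤ 2 where Z ≤ −2 is needed, so the primary endpoint as written classes nearly every patient in both arms as a case

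*Protocol article*

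**What the plan says.** Under Primary outcome measures, the article states the aim ("Our primary objective is to assess the incidence of POCD 7 days after surgery") and says what the classification uses: "The data of each patient consists of preoperative and postoperative data". Z-scores are then computed by a cited method; no formula, reference group or sign convention is printed. The decision rule is "The positive result is at least one" Z-score "≤ 2 (Wechsler word recall, visual reproduction, number symbols, number width) or ≥ 2 (number lines"). One test beyond its threshold is therefore enough, out of five.

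The Abstract, Objectives and Participant timeline sections name the endpoint or the tests but give no threshold. This sentence is the only place where the rule appears.

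Under Sample size, the trial is planned on the basis that "the incidence rate of POCD after a major surgery was 25% [12], and the estimated application of probiotics could reduce it to 10"%. The Discussion quotes reported POCD incidences of 9.9% to 46.1%.

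**The concern.** On word recall, visual reproduction, digit symbol and digit span a lower score is worse. The number-connection test runs the other way. The printed inequalities follow that pattern: ≤ for the first four, ≥ for the last. A rule meant to pick out the bad tail on every test would have thresholds of −2 and +2. As printed, the first threshold is +2, which takes in the whole distribution except its best 2.3%.

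Applied literally, the rule classes a patient as a case unless all four of these scores improve by more than 2 SD. Incidence would sit at the ceiling in both arms, and the planned chi-square or Fisher test could not detect an effect of any size.

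**Working it through.** **Inputs from the article.** The rule: any of four tests with Z ≤ 2, or number connection with Z ≥ 2 (Primary outcome measures). Planned rates 25% and 10%; alpha 0.05, power 0.80; 100 per group before dropout and 110 after (Sample size). Two-sided chi-square or Fisher test (Statistical analysis).

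**Assumptions.** Z-scores are standard normal in a patient with no true decline. Correlations r between tests, oriented so that they agree on which direction is worse, range from 0 to 0.9. The article gives neither.

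**Step 1: the plan's own figure.** For 25% vs 10%, with pooled proportion 0.175:

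n = [1.96 × √(2 × 0.175 × 0.825) + 0.8416 × √(0.25 × 0.75 + 0.10 × 0.90)]² / 0.15² = (1.4965)² / 0.0225 = 99.5, rounded up to 100 per group.

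This matches the article. The sample size is sound for those rates; the question is whether the printed rule can produce them.

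**Step 2: one test.** P(Z ≤ 2) = Φ(2) = 0.9772. P(Z ≤ −2) = 0.0228.

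**Step 3: the whole rule, no true decline.** With independent tests a patient escapes the printed rule only if all four scores exceed 2 and number connection is below 2: 0.02275⁴ × 0.97725 = 2.6 × 10⁻⁷. Under the signed rule (≤ −2 on four, ≥ 2 on the fifth) the positive share is 1 − 0.97725⁵ = 10.9%. Correlated cases come from numerical integration over a shared normal factor.

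| r | Printed rule | Signed rule |
|---|---|---|
| 0 | >99.9999% | 10.9% |
| 0.3 | 99.99% | 9.6% |
| 0.5 | 99.94% | 8.4% |
| 0.7 | 99.7% | 6.8% |
| 0.9 | 99.2% | 4.7% |

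**Step 4: the planned rates.** Find the mean shift at which the signed rule gives 25% or 10%, then apply the printed rule to the same patients.

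| r | Signed 25%: printed rule gives | Signed 10%: printed rule gives |
|---|---|---|
| 0 | >99.9999% | >99.9999% |
| 0.5 | 99.996% | 99.956% |
| 0.9 | 99.966% | 99.734% |

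The shifts needed are all under 1 SD, so 25% and 10% are attainable under the signed rule. Under the printed rule, even at r = 0.9, the expected number of patients without POCD among 110 is 110 × 0.00034 = 0.04 in the control arm and 110 × 0.0027 = 0.3 in the probiotic arm.

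**Step 5: power at the ceiling.** Take 99.9% vs 99.5% with 100 per group, a wider gap than any in Step 4. The normal approximation gives about 7%, against the planned 80%. That approximation flatters the test this close to 100%: summing binomial probabilities over all 2 × 2 tables gives about 0.15% for the uncorrected chi-square test and less for Fisher's test.

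**Step 6: the other sign convention.** Suppose a positive Z meant decline on every test. The ≥ 2 for number connection would then be right, and the ≤ on the other four would point the wrong way. The printed rule fails under this reading too.

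**The case against.** The strongest reply is that this is a lost character. The text was converted from PDF, and a minus sign could have dropped out there or in typesetting. The text at hand contains no other negative number to test that against. The ≤, ≥ and × symbols and the en dashes do survive, so loss in conversion is possible but not shown.

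The second reply is that the intent is plain. The opposing inequalities, the planned 25% and 10%, and the incidences in the Discussion all rule out a near-100% endpoint. A literal derivation would be noticed at once, and nothing at hand shows that any patient was classified with +2. This stands: the damage arises only if the text is followed as printed.

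The third reply is that the Z-score method comes from a cited source, so a wrong sign is the likely diagnosis rather than the only one. That also stands as far as the diagnosis goes, and the correction should be checked against the full protocol and that source. It does not rescue the rule: the article prints its own threshold, and Step 6 shows that it fails under either convention.

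Finally, the calculation assumes standard-normal Z-scores. If every mean moved 1 SD towards improvement, the printed rule would still class 97.9% (r = 0.5) to 99.9% (r = 0) of patients as cases.

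**Conclusion.** The concern holds: the definition is wrong as written. With no true decline, the printed rule makes more than 99.9% of patients POCD cases for correlations from 0 to 0.5, and 99.2% even at 0.9. The plan assumes 25% and 10%. With −2 on the four tests, the no-decline rate is 8.4% to 10.9% for correlations from 0 to 0.5, a scale on which the planned rates make sense.

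The figures rest on approximately standard-normal Z-scores and assumed correlations, but the conclusion does not depend on their exact values. The intended threshold is very probably −2. The point must still be fixed before analysis, because this sentence alone decides who counts as a primary-outcome event. The sample size calculation is not affected.

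**What to change.** Amend the definition to: POCD is present if Z ≤ −2 on at least one of word recall, visual reproduction, digit symbol and digit span, or Z ≥ +2 on number connection. Equivalently, reverse the sign of the number-connection score and use Z ≤ −2 for all five tests.

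Before issuing the correction, confirm the sign convention against the full protocol and the cited Z-score method, and state that convention beside the rule. Check that the derivation code carries the same signed thresholds. Recruitment began in December 2019, so re-check the status of any patient already classified.

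The cost is a one-line correction and a code check. It needs no extra patients, visits or assessments, and 110 per group is unchanged.

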### Secondary outcome measures

Secondary outcomes comprise the following:Incidence of POD

Postoperative delirium will be assessed 7 days after surgery using the Confusion Assessment Method (CAM), which includes acute onset, inattention, disorganized thinking, and abnormal consciousness. The diagnosis of delirium by CAM requires the presence of features 1 and 2 and either 3 or 4 (Table 2).2)Cognitive status 1 month after surgery

The cognitive status will be determined based on a telephone interview and will be evaluated via TICS-m in 1 month after surgery.

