### Participant timeline

Figure 1 presents the schedule for enrollment, interventions, assessments, and visits of participants.

Cognitive function assessment: 1 day before operation: Mini-Mental State Examination (MMSE) screening, digit span test, digit symbol test, Wechsler Memory Scale (WMS), visual regeneration, and digital connection test will be performed. 7 days after operation or before discharge: digit span test, digit symbol test, WMS, visual regeneration, and digital connection tests will be performed again. 7 days after operation: POD will be assessed using the CAM, which includes acute onset, inattention, disorganized thinking, and abnormal consciousness. The diagnosis of delirium by CAM requires the presence of features 1 and 2 and either 3 or 4. Table 2 presents the specific content.

**Table 2 Tab2:** Specific content of the Confusion Assessment Method

The Confusion Assessment Method (CAM)	
Feature 1	Acute change in mental status with a fluctuating course Is there evidence of an acute change in mental status from the patient’s baseline? Did this behavior fluctuate during the past day, that is, tend to come and go or increase and decrease in severity? This feature is usually obtained from a family member or nurse and is shown by positive responses
Feature 2	Inattention Do the patients have difficulty focusing attention, for example, being easily distractible, or having difficulty keeping track of what was being said?
Feature 3	Disorganized thinking This feature is shown by a positive response to the following question: Was the patient’s thinking disorganized or incoherent, such as rambling or irrelevant conversation, unclear or illogical flow of ideas, or unpredictable switching from subject to subject?
Feature 4	Altered level of consciousness Overall, how would you rate this patient’s level of consciousness? (alert [normal], vigilant [hyperalert], lethargic [drowsy, easily aroused], stupor [difficult to arouse], or coma [unarousable])

The diagnosis of delirium by CAM requires the presence of features 1 and 2 and either 3 or 4

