Before surgery, the doctor will conduct medical visits for up to 40 min and complete the scale for each patient; furthermore, they will inform the patients that they will be followed up and observed for several consecutive days after surgery. If necessary, the doctor will communicate with the patient through WeChat to understand their latest situation in addition to communicating through phone calls. One day before surgery, the anesthesiologist will record each patient’s general information, including sex, years of education, BMI, dietary habits, history of disease, medication, and surgery. During surgery, blood pressure fluctuations are maintained within 20% of the baseline blood pressure level. Anesthesiologists will record the volume of infusion, estimated blood loss, and urine output and assess the need for a blood transfusion. Similarly, the duration of surgery, anesthesia, and hospital stay after surgery are recorded. After surgery, an analgesia pump will be used for intravenous self-analgesia (uniformly prepared by the pharmacy). Patient-controlled analgesia and or nerve block would be used for postoperative analgesia in all patients to maintain a VAS score of less than 3. The PCIA pump includes the following analgesics: sufentanil citrate 100 μg and flurbiprofen axetil 100 mg which are prepared into 0.9% sodium chloride, in a total volume of 100 ml. All patients receive a 1.5 ml on-demand bolus with a lockout interval of 15 min. The infusion was started immediately after suturing the skin incision and lasted 48 h. We use morphine as rescue drug, which is given according to the patient’s pain situation. At the same time, the drug dosage of the patient’s analgesia pump used and morphine dosage are recorded. Three months after operation, the same doctor will call the patient again for follow-up. All data collected during this clinical study will be entered and/or filed in the patients’ CRFs. The patients’ study participation must be documented appropriately in the CRF with their study number, subject number, date of subject information, informed consent, and date of each visit. Source data will be filed according to the GCP guidelines. The data manager will be responsible for data processing, following the sponsor’s standard operating procedures.

Regular monitoring will be conducted to ensure that the data are adequate, accurate, and complete. The database will be locked only after the completion of quality assurance procedures.

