In our animal experiment, the probiotic regimen of mice refers to the study by Rachmilewitz et al. [48], i.e., from 7 days before surgery to 10 days after surgery. Currently, clinical studies are mainly focused on major abdominal surgery. There is no uniformity in the preoperative administration plan of probiotics, which is given approximately 10 days before surgery or even after surgery [49–51]. These studies have proven that probiotics can effectively reduce postoperative infection rates, fight against intestinal bacterial overgrowth and clinical symptoms, and reduce postoperative complications and hospital stay duration [52]. There are few clinical studies on probiotics for POCD. Wang et al. [47] gave probiotics to patients who underwent noncardiac surgery from the time of admission to discharge and found that probiotics significantly improved postoperative cognitive impairment. In this study, our research participants are elderly patients who will undergo orthopedic elective surgery. As we can only receive official confirmation of a surgical operation 1 day before surgery, we set the preoperative administration route as oral 1 day before surgery. Furthermore, because the average hospital stay duration after surgery is 5–8 days, we set the administration time for patients after surgery as 6 days. Thus, we maximized the duration of oral administration of probiotics for hospitalized patients, which may benefit these patients.

Patients in our study need to receive routine antibiotic treatment, particularly cephalosporins, on the operation day and for 3 days after surgery. To avoid interference with the clinical work of surgeons, we did not limit the use of antibiotics after surgery. Previous studies have reported that probiotic treatment in the presence of antibiotics provides protection against postoperative infectious complications [53–55]. Thus, short-term antibiotic use (several days) is not an obstacle to perioperative probiotic administration. As this is a randomized controlled experiment, the difference in antibiotic treatment would be minimized due to randomization. However, perioperative probiotic treatment may provide improved protection against postoperative cognitive impairment in the absence of antibiotics.

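### The delirium outcome is named an incidence, but the text gives only a day-7 CAM, which measures delirium present around day 6–7 and has no rule for patients discharged earlier

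*Protocol article*

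**What the plan says.** Under Secondary outcome measures the first outcome is named incidence of POD and is measured as follows: "Postoperative delirium will be assessed 7 days after surgery using the Confusion Assessment Method (CAM". Participant timeline gives the same time point: "7 days after operation: POD will be assessed using the CAM". The Abstract also places the CAM at 7 days, and Objectives again speaks of incidence at 7 days. No section of the text names a CAM on an earlier postoperative day.

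The diagnostic rule is "The diagnosis of delirium by CAM requires the presence of features 1 and 2 and either 3 or 4". Feature 1 in Table 2 is an acute change with a fluctuating course, and one of its two questions is "Did this behavior fluctuate during the past day".

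The cognitive battery is timed differently. Participant timeline has "7 days after operation or before discharge: digit span test, digit symbol test", and Primary outcome measures has "7 days after operation or on the day of discharge by the following scales". The Discussion states that "the average hospital stay duration after surgery is 5–8 days". Data collection and management says patients will be "followed up and observed for several consecutive days after surgery", without naming the CAM or any delirium screen.

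**The concern.** An incidence counts every patient who has at least one episode in the interval from surgery to day 7. One assessment near the end of that interval counts only those whose delirium is still present, or has fluctuated within about a day. For a condition that the protocol itself describes as acute and fluctuating, the two quantities can differ a good deal.

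Three things are at stake. The reported figure would understate incidence. Fewer events would reduce an already limited ability to show a difference, so a null result would say little about delirium over the first week. Patients who go home before day 7 have no stated CAM, so who is assessed depends on discharge timing. If more than 5% of CAM results are missing, the rule under Additional analyses would replace them with a group mean, which has no meaning for a yes/no diagnosis.

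**Working it through.** **1. The plan's own figure.** The only sample size is for POCD: 25% versus 10%, two-sided alpha 0.05, power 0.80. With the pooled-variance formula and d = 0.15:

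n = [1.96·√(2 × 0.175 × 0.825) + 0.8416·√(0.25 × 0.75 + 0.10 × 0.90)]² / 0.15² = (1.053 + 0.443)² / 0.0225 ≈ 99.5, so 100 per group.

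This reproduces the stated 100. No rate, sample size or power is stated for POD, so what follows in steps 3 to 5 is illustration under assumptions.

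**2. Label against measure.**

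| Item | Text |
|---|---|
| Name of outcome | Incidence of POD |
| CAM time point | Day 7 (Abstract, Participant timeline, Secondary outcome measures) |
| Window | Past day, for the fluctuation question in Feature 1 |
| Discharge alternative, cognitive tests | Yes |
| Discharge alternative, CAM | None stated |
| Average postoperative stay | 5–8 days |

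An episode that starts on day 1 and is over by day 3 is part of the incidence but would not be expected to turn a day-7 CAM positive. An episode that starts on day 2 and lasts to day 7 would be counted.

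**3. Share of episodes captured (assumed onset and duration).** With onset on day d and exponential duration of mean m days, the chance that an episode is still present at day 6 is e^(−(6−d)/m).

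- Onset on days 1/2/3 in 40/40/20%: 0.4e^(−5/m) + 0.4e^(−4/m) + 0.2e^(−3/m) = 0.02, 0.13 and 0.25 for m = 1, 2 and 3.
- Onset spread evenly over days 1–5: [e^(−5/m) + e^(−4/m) + e^(−3/m) + e^(−2/m) + e^(−1/m)] / 5 = 0.12, 0.28 and 0.41 for m = 1, 2 and 3.

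With an assumed 15% true incidence, 0.15 × 110 = 16.5 patients per arm would have an episode. The first pattern leaves 0.3 to 4.2 of them visible and the second 1.9 to 6.8. The answer depends heavily on onset. The first pattern allows no onset after day 3, so its low capture is partly built in.

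**4. Effect on power (assumed).** Relative risk 0.4 (the ratio 10%/25% used for POCD), 100 per arm, the same capture in both arms, and power = Φ{[d√n − 1.96√(2p̄q̄)] / √(p₁q₁ + p₂q₂)}. For 15% versus 6%: (0.900 − 0.850) / 0.429 = 0.117, so power is 0.55.

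| True POD in controls | Full capture | Half | Quarter |
|---|---|---|---|
| 10% | 38% | 21% | 12% |
| 15% | 55% | 30% | 17% |
| 25% | 80% | 47% | 25% |

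**5. Share home before day 7 (assumed normal stay, SD 1.5 days).** Φ((7 − mean)/1.5) = 91%, 75%, 50% and 25% for means of 5, 6, 7 and 8 days. At a mean of 8, an SD of 1 to 2 days gives 16% to 31%. Under these assumptions the group without a stated CAM is not negligible anywhere in the quoted range.

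**The case against.** The strongest reply is that the schedule cannot be seen. The text refers to Fig. 1 for assessments and the figure is not available. No sentence says that the CAM is done only once, and observation over several consecutive days is compatible with repeated screening. The stated objective could also be read as a seven-day horizon. This limits certainty, but it does not remove the point: each dated mention of the CAM says day 7, and the passage on daily observation names no delirium tool.

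Several stronger readings are tempting and are not supported:

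- A reader might infer that all delirium on days 1–5 is missed. Delirium persisting to about day 6–7 would be detected. The one-day window belongs only to the fluctuation question; the acute-change question has none.
- A reader might infer that discharged patients are excluded from the CAM. The protocol does not say so. It makes no provision for them, which is a gap and not an exclusion.
- A reader might infer that a CAM at home would fail for lack of a nurse informant. Table 2 accepts a family member equally.
- A reader might infer that the outcome cannot show an effect. Incomplete capture lowers power; it does not abolish it. Power at 10–15% true POD is only about 38–55% even with full capture, so better ascertainment alone would not make a null result conclusive.

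It also stands that recruitment began in December 2019 and was due to end about December 2023, while the article appeared in February 2023. About 38 of 48 months had passed, so a late change in ascertainment has a real cost.

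**Conclusion.** The concern holds in this form. As the text stands, the outcome named incidence of POD is measured by a CAM at day 7 and is close to a prevalence around day 6–7. Episodes resolved earlier are not counted, so incidence is understated and the outcome is poorly able to show an effect. Patients discharged before day 7 have no stated CAM, although the cognitive tests have a discharge alternative.

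The size of the loss cannot be calculated from the documents. The capture shares (2% to 41% across the patterns tried), the power figures and the discharge shares rest on assumed rates, onset, duration and length of stay. They show direction and sensitivity, not an estimate. The conclusion also assumes that the missing Fig. 1 adds no further CAM. The primary outcome is unaffected, so this is a change that should be made to a secondary outcome and not a threat to the main analysis.

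**What to change.** **For all patients:** state the CAM time as day 7 or the day of discharge, whichever is first, in line with the cognitive battery. Rename the outcome *delirium present on day 7 or at discharge*, and make no claim about incidence in the objectives or the report. Record the actual day of the CAM, and report by arm how many patients have none; those already discharged without one cannot be recovered.

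**For patients still to be enrolled (optional):** add a daily CAM by the same blinded assessors from day 1 to day 7 or discharge, count any positive CAM as POD, and report this separately from the single-assessment outcome.

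If Fig. 1 already contains repeated CAM assessments, the text should be corrected to match it and the incidence label can stay, with any positive CAM as its definition.

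**Cost:** the first part needs a protocol amendment and a change of wording. Its price is a weaker claim and an assessment day that varies with discharge. The daily CAM adds a few minutes per patient per day and extra CRF lines. It also creates two ascertainment methods, before and after the amendment, and these must not be pooled as one outcome. With most of the recruitment period already past, the subgroup with daily data may be small.
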